# Efficiency of atorvastatin on in-hospital mortality of patients with acute aortic dissection (AAD): study protocol for a randomized, open-label, superiority clinical trial

**DOI:** 10.1186/s13063-021-05237-1

**Published:** 2021-04-14

**Keywords:** Acute aortic dissection, Atorvastatin, Statins, In-hospital mortality

## Abstract

**Background:**

Dyslipidemia and local inflammation at sites of lipid deposition on blood vessel walls have been demonstrated to be risk factors for patients with acute aortic dissection (AAD). Statins have anti-inflammatory and lipid-lowering effects, which suggest that statins may play an important role in the prevention and treatment of AAD. Some retrospective studies show that statins can protect patients with aortic dissection. However, the effect of statins on the survival of AAD patients has been scarcely investigated, especially in randomized trials. In this study, we will perform a randomized clinical trial to understand whether statins can reduce in-hospital mortality of AAD patients.

**Methods:**

A total of 384 subjects diagnosed with AAD in the First Affiliated Hospital of Shantou University Medical College will be recruited. Participants will be randomly divided into an atorvastatin-treated or control group. The primary outcome will be the in-hospital mortality at 30 days.

**Discussion:**

This study is designed to verify the efficacy of atorvastatin on reducing in-hospital mortality of patients with AAD. The aim is to provide a new means of improving survival as a complement to conventional drug therapy.

**Trial registration:**

Chinese Clinical Trials Registry ChiCTR1900023515. Registered on 1 June 2019.

## Background

Acute aortic dissection (AAD) is relatively uncommon but is considered a life-threatening, potentially fatal condition [1]. A recent International Registry of Acute Aortic Dissection (IRAD) study shows that 87–90% of AAD is treated surgically, and drug treatment only accounts for 7–8%. Nevertheless, the IRAD study indicates that in-hospital surgical mortality for AAD remains approximately 20% [2], indicating improvement of the long-term outcome of patients with aortic diseases requires further optimization [3]. However, in addition to strict control of blood pressure and heart rate, the effect of other drugs on AAD is still controversial and lacking strong clinical evidence.

Dyslipidemia and atherosclerosis are important risk factors for AAD [4]. Lipid deposition in the vascular wall can lead to local inflammation [5] and promote the release of inflammatory mediators that destroy the vascular wall, leading to aortic dissection (AD) [6]. Statins are classical drugs for lowering low-density lipoprotein cholesterol (LDL-C) levels, and are both anti-inflammatory and anti-atherosclerotic [7], suggesting that statins may delay progression of AAD.

Recent reports have shown that statins have anti-inflammatory effects and can decrease morbidity and mortality following surgical repair of aneurysms in patients with abdominal aortic aneurysms and aneurysm expansion [8–11], and several experimental studies demonstrate the protective effect of statins [12–14]. A retrospective study showed that patients with AAD who used statins had a significantly better prognosis than those who did not [15]. Also, a prospective and randomized comparative study of patients with uncomplicated acute type B aortic dissection (ABAD) showed that pitavastatin treatment has a suppressive effect on aortic arch dilatation [3]. However, a retrospective review points out that statins do not improve in-hospital and long-term outcomes in patients with Stanford B aortic dissection treated with endovascular aortic repair [16]. Although these studies have explored the effects of statins on aortic disease [3, 14–17], the results remain controversial. The aim of this randomized clinical trial study is to understand the efficiency of atorvastatin on in-hospital mortality of patients with AAD. We propose that AAD patients treated with statins will have lower in-hospital mortality than patients without.

## Methods

### Study design

This prospective trial was designed as a single-center randomized, open-label, superiority clinical trial with patients allocated 1:1, to be conducted at the First Affiliated Hospital of Shantou University Medical College, Shantou, Guangdong, China. The protocol was designed according to the Standard Protocol Items: Recommendations for Interventional Trials (SPIRIT) 2013 Statement.

### Study objectives and hypothesis

The primary objective of this trial is to assess the effect of statins on in-hospital mortality of AAD patients. The secondary objective is to determine the incidence of liver dysfunction (alanine aminotransferase (ALT)/aspartate aminotransferase (AST) > 3 times the normal value). We predict that AAD patients treated with statins will have lower in-hospital mortality than patients without.

### Ethics issues

The present study protocol was approved by the Committee of Ethics of the First Affiliated Hospital of Shantou University Medical College (Number: 2019038).

### Participant recruitment

For the clinical study registered on 1 June 2019, participants will be screened after registration and will be diagnosed for AAD by means of computed tomography angiography (CTA) [18] in The First Affiliated Hospital of Shantou University Medical College. Patients who may qualify for the study will be referred by an emergency physician, community hospital doctor or member of a healthcare hospital research team. A research team consists of clinicians who are familiar with AAD diagnosis and treatment. In addition, the researchers will receive appropriate training regarding all the relevant information pertaining to the study. Those who are willing to take part in the study will be carefully evaluated according to the inclusion and exclusion criteria.

### Criteria

Inclusion criteria:
Patient agrees to cooperate with all study procedures;Age > 20 years old;Physical status permits oral medication;Cholesterol < 5.1 mmol/l, triglyceride < 1.7 mmol/l;Provision of written informed consent.

Exclusion criteria:
Liver dysfunction: alanine aminotransferase (ALT)/aspartate aminotransferase (AST) > 3 times the normal value;Breast-feeding or pregnancy (for women of child-bearing age, the human chorionic gonadotropin level will also be measured before drug administration);Previous history of coronary atherosclerotic heart disease;Statins used within 6 months before inclusion;Participation in another clinical trial within 6 months;Allergy to statins.

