### Withdrawal

Patients may be withdrawn from the study for any of the following reasons:
They may choose to withdraw for any reason;They have abnormalities in ALT/AST (> 3 times upper limit of normal) after drug administration;The patient wants to accept other kinds of statins;Other situations: based on the investigator’s discretion, the patient is no longer eligible for the study for any reason.

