### Data collection and management

At enrollment, we will collect the demographic information of the participants, including age, gender, blood pressure, heart rate, previous disease history, medical history, smoking history. Leukocytes, hemoglobin, platelets, C-reactive protein, cholesterol, triglycerides, creatinine, uric acid, glycosylated hemoglobin, AST, and ALT will be measured at baseline, the 7th, and 13th day. Here, 2 mL fasting venous blood will be taken for measurement in the morning. All these blood parameters will be collected. At discharge or death of the patient, data will be collected on patient status, medication in the hospital, diagnosis and comorbidity. All data will be transferred to a database by duplicate entry using EpiData software (Denmark, version 3.1), and will be stored in the scientific research platform of the First Affiliated Hospital of Shantou University Medical College, which is a secure server with limited access and supported for anonymity, analysis and review.

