### Outcome measurements

The primary outcome of this study will be the in-hospital mortality at 30 days. We will calculate in-hospital mortality by counting all-cause death. Secondary outcome will be the incidence of liver dysfunction, as measured through ALT and AST at the 7th and 13th day. The expected trial target is fewer deaths in the statin group compared to the control group.

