### Statistical and analytical plans

A comprehensive statistical analysis plan will be prepared before database locking. All analyses will be conducted according to the intention-to-treat (ITT) principles. The primary outcome is binary, it will be expressed as frequency and percentage, a chi-square test will be used to analyze. All statistical analyses will be two-sided, and statistical significance will be set at 0.05. Continuous data such as blood pressure, heart rate and blood parameters, will be presented as mean ± SD; Categorical data, such as previous disease history and smoking history, will be expressed as frequency and percentage of patients in each category. The Kolmogorov-Smirnov test will be used to confirm the normality of the distribution of continuous data, if *P* < 0.05 indicates the data is not normally distributed, advanced raw data conversion (such as logarithmic conversion) will be performed to see whether the data conform to a normal distribution. If not, the rank-sum test will be selected. Otherwise, Student’s *t* tests will be used for continuous data. The chi-square test will be used for categorical data. Survival curves will be determined by the Kaplan-Meier method for survival analysis. The difference in changes between the groups will be analyzed using both Student’s *t* test and analysis of covariance to adjust for the baseline values. A *p* value of < 0.05 will be used to indicate statistical significance. The missing data will be handled by using Mean/Mode Completer. If the missing data is numerical, it will be filled according to the average value of all other objects; if the missing data is non-numerical, then it will be supplemented by the value with the most frequent value of all other objects according to the mode principle in statistics. SPSS statistical software (SPSS Inc., Chicago, IL, USA, version 23) will be used for statistical analysis.

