### Safety and adverse events

The most common AEs related to the intake of atorvastatin are expected to be liver enzyme abnormalities, muscle pain, nausea, and diarrhea. Participants showing any adverse event will be treated appropriately by doctors, and the project will cover the cost of adverse events. Adverse reactions will be checked at every visit. For any AE that occurs, all details, including the time of occurrence, symptoms and signs, degree, duration, laboratory findings, treatment, outcomes, and causal relationship with the treatment, will be recorded in the CRF. Serious AEs will be reported to the Research Ethics Committee within 24 h, which will decide whether any additional measures should be taken. The total number of patients with AEs related to the study drug (certain, probable, possible) and the total number of patients with AEs leading to discontinuation of study treatment will be summarized.

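### The liver outcome shares its 3-times cut-off with the entry criterion, so events depend strongly on baseline, yet the stated test is an unadjusted chi-square: a small, avoidable loss of precision, not a bias

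*Protocol article*

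**What the plan says.** All references are to the protocol article; no separate SAP is at hand.

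- **Criteria:** patients are excluded for "Liver dysfunction: alanine aminotransferase (ALT)/aspartate aminotransferase (AST) > 3 times the normal value".
- **Study objectives and hypothesis:** "The secondary objective is to determine the incidence of liver dysfunction (alanine aminotransferase (ALT)/aspartate aminotransferase (AST) > 3 times the normal value". The multiple is the same as at entry, and no condition refers to the patient's own starting value.
- **Outcome measurements:** "Secondary outcome will be the incidence of liver dysfunction, as measured through ALT and AST at the 7th and 13th day". No other secondary outcome is named.
- **Data collection and management:** "AST, and ALT will be measured at baseline, the 7th, and 13th day", so the baseline values will exist for analysis.
- **Statistical and analytical plans:** "The chi-square test will be used for categorical data". Analysis of covariance with baseline adjustment is stated for differences in changes between groups, which does not reach a yes/no outcome. The section also says that a full SAP will follow before database lock.

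**The concern.** Everyone enters at or below 3 times normal, and an event means being above it later. A patient who enters close to the line needs only a small rise; a patient who enters at an ordinary value needs a several-fold rise. Under Limitations, surgical patients are often enrolled only after the operation, once a normal diet is restored, and all patients are enrolled around an acute illness. Some may well enter with raised enzymes, although the article gives no figures.

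A baseline value that predicts the outcome this strongly is worth using. An unadjusted chi-square leaves that predictable variation in the comparison. Limitations and Discussion both make a higher-dose follow-on study depend in part on the results suggesting safety. In a safety comparison, noise makes a real difference harder to see.

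**Working it through.** **1. Distance to the line.** The smallest rise that makes an event is 3.0 / baseline. Entry at 2.9 times normal gives 3.0/2.9 = 1.034, a rise of just over 3%. Entry at 0.7 gives 3.0/0.7 = 4.29, more than fourfold.

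**2. Plan figures.** The article states no expected rate, power or baseline distribution for the liver outcome, so there is no figure to reproduce. Only the 192 patients per arm (Sample size) is used below. Everything else in steps 3 to 5 is an assumption.

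**3. Assumed model.** Baseline *b* and one follow-up value *y*, in ULN units, are log-normal with median *m*, log-SD 0.7 and correlation *r*. Entry requires *b* ≤ 3; an event is *y* > 3; there is no drug effect. The article's normal value is read as ULN. One enzyme and one follow-up value stand in for two enzymes at two visits. Given *b*, ln *y* is normal with mean ln *m* + *r*(ln *b* − ln *m*) and SD 0.7√(1 − *r*²). With *m* = 0.7 and *r* = 0.6 the SD is 0.56:

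- *b* = 2.5: mean = −0.357 + 0.6 × (0.916 + 0.357) = 0.407; (1.099 − 0.407)/0.56 = 1.24; risk about 11%.
- *b* = 0.7: mean = −0.357; (1.099 + 0.357)/0.56 = 2.60; risk about 0.5%.

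Averaged over entry ranges, risk is about 10% for entry at 2 to 3 times ULN and 0.3% for entry below ULN.

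**4. Where the events come from** (simulation of the model in step 3):

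| *m* | *r* | Incidence | Events per 192 | Patients above ULN at entry | Their share of events | Events not doubling baseline | Events with rise under 25% |
|---|---|---|---|---|---|---|---|
| 0.7 | 0.6 | 1.5% | about 3 | 29% | 84% | 37% | about 5% |
| 0.7 | 0.4 | 1.7% | about 3 | 29% | 65% | 22% | about 2% |
| 1.0 | 0.6 | 4.2% | about 8 | 47% | 89% | 42% | about 5% |
| 0.7 | 0.8 | 1.1% | about 2 | 29% | 98% | 66% | about 11% |

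Over 18 settings of this model (median 0.5 to 1.0, log-SD 0.5 to 0.7, correlation 0.4 to 0.8), entrants above ULN supplied 55% to 99.9% of events, and rises under 25% were 2% to 20%. A different model was run over 48 scenarios: median 0.5, 0.8 or 1.2; log-SD 0.5 or 0.8; a sixfold injury in 1% or 3%; the worse of two visits. Rises under 25% were 0% to 48% of events there, never a majority. Entrants at 2.5 to 3 times normal supplied more than half of events in only 3 of the 48.

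**5. What adjustment gains.** The plain chi-square was compared with a logistic score test adjusted for log baseline, at 192 per arm under the step 3 model, for (*m*, *r*) = (0.7, 0.6), (0.7, 0.4), (1.0, 0.6) and (1.0, 0.8), with 4,000 simulated trials per setting. With no drug effect, rejection was 4.2% to 5.9% for the chi-square and 4.5% to 5.6% for the adjusted test. With a sixfold injury in 5% of the statin arm, power went from 46.7 to 48.0, 45.7 to 45.8, 35.4 to 37.1 and 42.2 to 45.3%. With a uniform 1.5-fold shift, it went from 65.0 to 69.0, 65.7 to 66.5, 91.5 to 93.3 and 94.0 to 97.2%. The gain is mostly 0 to 3 points, 4 in one setting, with no loss in any.

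**6. Redefining the outcome instead.** Adding a multiple-of-baseline condition at 192 per arm gained 5 to 12 points of power under the 5% sixfold-injury model but lost 3 to 7 under a uniform shift. That is a trade-off, not a clear improvement.

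**The case against.** The case against has real force. Allocation is 1:1, blocked and stratified by dissection type, so patients near the line are expected equally in both arms. Crossings unrelated to the drug are noise, the chi-square remains valid when there is no effect, and chance imbalance is ordinary sampling error that the test already allows for. Any threshold outcome is reached more often by patients who start near it. Every rate above is assumed. A SAP is promised, and an adjusted secondary analysis could well sit there. With about three events per arm, an adjusted model is sparse and needs care. All of this stands, and it limits the point to a loss of precision. What remains is that the article already names the test for categorical data and confines baseline adjustment to changes.

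A reader might infer more, but the article does not support it:

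- **That trivial rises in patients just below the line dominate the comparison.** Entrants above ULN supply most events in the step 3 model, but many of those are substantial rises. A move from 1.2 to 3.1 times ULN is one of them.
- **That the plan ignores baseline.** Exclusion makes every event a new crossing, baseline is measured, and changes are to be adjusted for it.
- **That AST rises from muscle would be miscounted as liver injury.** The article lists "liver enzyme abnormalities, muscle pain, nausea, and diarrhea" as expected effects but does not say why AST rises; the inference rests on outside knowledge.
- **That the safety conclusion rests on this outcome alone.** All-cause mortality, all adverse events, drug-related events and events leading to discontinuation are also recorded.

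**Conclusion.** The point holds in a limited form. The shared cut-off is neither a contradiction nor a source of bias between arms. It does make baseline enzyme a strong predictor of the only secondary outcome, and the stated test leaves that predictor unused although it is collected. On assumed inputs, adjustment keeps the type I error near 5% and adds about 0 to 3 points of power. The size depends on the baseline distribution, the baseline to follow-up correlation and the form of any drug effect, none of which the article gives. Confidence is high on what the article states and moderate on the size. The improvement is small and nearly free.

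**What to change.** 1. Keep the stated outcome (above 3 times normal at day 7 or 13) as it is.
2. Replace the plain chi-square for this outcome with an arm comparison adjusted for log baseline enzyme, using a method suited to few events, such as a score test or a correctly implemented penalised logistic model.
3. As support, tabulate events by arm and by baseline (at or below ULN versus above ULN), and report how many at least doubled the patient's own baseline. This shows whether events are new rises or small crossings without changing the outcome.

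The forthcoming SAP can carry this. Because the trial is open-label and its analysts are not blinded (Blinding), the wording should be fixed before anyone examines liver results by arm.

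The cost is wording and a slightly less simple analysis that must allow for sparse events. No visit, blood sample or patient is added.

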### Informed consent

Prior to enrollment, trained researchers will introduce the objective and main aspects of the trial to the patients. Patients will also receive information sheets and then be able to have an informed discussion with the participating consultant. Patients will also be informed of the probable benefits and potential risks and assured that participation is entirely voluntary. Patients who meet all of the inclusion criteria and none of the exclusion criteria will be enrolled after providing written informed consent. The personal information of all participants will always be kept confidential.

### Randomization and allocation

According to the order of the participants enrolled, they will be randomly assigned to the control or statin group by using a corresponding random number and envelope method for allocation concealment (patients will be assigned to a corresponding group according to the allocation sequence in an envelope that will be distributed to the research implementation personnel after the allocation sequences are packed in an opaque envelope by separate staff). Balance in allocation across the study participants will be enhanced through stratification by the type of AAD (two types: type A, type B). To avoid the imbalance caused by simple randomization, we introduce block randomization. The block length was 4 with two groups in this study (statins group and control group). The allocation sequence will be generated at a 1:1 (statin/control) ratio using the random number generator in the SPSS statistical software package (SPSS Inc., Chicago, IL, USA, version 23) (Fig. 1).

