### Blinding

This is an open-label trial. Trial participants, investigators, care givers, outcome assessors, and date analysts are not blinded to group assignment.

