### Interventions

Participants will be randomized into two equal groups: statin (atorvastatin) or control group as soon as clinical conditions permit. The statin group will be required to take atorvastatin 20 mg daily (known to be a safe dose effective in lipid-lowering and anti-inflammatory activity [19–21]), and the control group will be required to not take statins during study period. Atorvastatin will be provided by Pfizer (New York, USA).

The scheduled duration of treatment is the duration of the hospital stay unless a serious adverse event occurs or the participant quits. The detailed study schedule is listed in Fig. 2.

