## Trial status

The version of this protocol is 2.0 (date 20201225). It is currently recruiting patients.

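### A single fixed block length of 4, published during recruitment into an open-label single-centre trial, undermines the concealment that the envelopes are meant to give

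*Protocol article*

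**What the plan says.** Under Randomization and allocation, the protocol article sets permuted blocks of one length: "The block length was 4 with two groups in this study (statins group and control group". The same section gives the ratio, "The allocation sequence will be generated at a 1:1 (statin/control) ratio", and the strata, "stratification by the type of AAD (two types: type A, type B". Concealment rests on envelopes, handed to the implementing staff "after the allocation sequences are packed in an opaque envelope by separate staff".

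Four other statements bear on how well this works:

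- Study design: the trial is a "single-center randomized, open-label, superiority clinical trial with patients allocated 1:1".
- Blinding: "Trial participants, investigators, care givers, outcome assessors, and date analysts are not blinded to group assignment".
- Interventions: patients are randomized to "statin (atorvastatin) or control group as soon as clinical conditions permit".
- Trial status: "It is currently recruiting patients".

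The article does not say that the block length varies or that it is kept from those who recruit.

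**The concern.** Concealment is meant to ensure that whoever decides on a patient's entry cannot foresee the arm. A sealed envelope protects the content of that envelope. It gives no protection against inference from earlier assignments when those are visible and the block structure is known. Here past assignments are open to the team, the stratum is the patient's own diagnosis, and the length is fixed and in print.

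Foreknowledge does harm only if entry can be influenced, and here there is some room for that. The time of randomization depends on the patient's clinical state, and eligibility requires fitness to take tablets. The Limitations section adds that surgical patients often wait until they can eat normally again, and that some die before then. The judgement about entry is therefore linked to early death, which is the primary outcome. A recruiter who knew the next arm could, without any bad intent, be influenced in whether or when to enrol a frail patient. Intention-to-treat analysis does not correct this, because the selection takes place before randomization.

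**Working it through.** **Inputs.** Block length 4, ratio 1:1, two strata (Randomization and allocation); 384 patients (Sample size). The protocol gives no figure for predictability.

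**The stated sample size, which is the denominator.** HR = ln(1 − 0.124)/ln(1 − 0.274) = 0.4135. Freedman events = (1.960 + 1.282)² × ((1 + 0.4135)/(1 − 0.4135))² = 61.0. N = 61.0/0.199 = 306.6, so 307, where 0.199 is the mean of 27.4% and 12.4%. Allowing for 20% loss, 307/0.8 = 383.75, so 384. Both stated figures reproduce, and nothing below changes them.

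**Assignments that are certain.** A 2+2 block has six equally likely orders: SSCC, SCSC, SCCS, CSSC, CSCS, CCSS. The fourth place is always forced. The third is also forced in SSCC and CCSS. Forced places: 2 + 1 + 1 + 1 + 1 + 2 = 8 of 24 = 33.3%. Over the whole trial, 384 × 1/3 = 128.

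**Best-guess success.** Rule: guess the arm with more places left in the block, and toss a coin if equal.

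- Place 1: 50%.
- Place 2: two of the three remaining places belong to the other arm, so 66.7%.
- Place 3: certain with probability 1/3, a coin toss with probability 2/3, so 1/3 + 1/3 = 66.7%.
- Place 4: 100%.

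Mean = (0.500 + 0.667 + 0.667 + 1.000)/4 = 70.8%, or 272 of 384, against 192 by chance.

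**Effect of stratification.** A separate tally for each type restores the same proportions, apart from an incomplete last block in each stratum.

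**If the length becomes known only part-way.** The ceiling is one third of the assignments still to come. The article does not say how many that is. As an assumed range: 128 if all 384 are exposed, 64 if half (192), 32 if a quarter (96).

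**With varying lengths.** These figures come from simulation (400 sequences of 192 assignments). The guesser knows which lengths are in use but not their order, and updates after every assignment. This is harsher than withholding the lengths altogether.

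| Lengths | Certain | Best guess correct |
|---|---|---|
| 4 only (exact) | 33.3% | 70.8% |
| 4, 6 | 5.5% | 69.2% |
| 4, 6, 8 | 2.1% | 68.0% |

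Varying the length removes most of the certainty but little of the guessing advantage.

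**The case against.** The strongest reply is that the calculation describes a capability, not something the document shows to happen. Participant recruitment describes referral from several sources, separate staff pack the sequences, and no statement says that recruiters know the length or keep a tally. That is correct, and the point has to be conditional. It still stands, because the article withholds nothing and puts the length in print.

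A reader might infer four stronger things that the documents do not support:

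- **That concealment is defeated.** Two thirds of assignments are not forced, and the first in each block remains a coin toss. Concealment is weakened.
- **That 128 assignments are in fact known in advance.** This is a ceiling. It needs a known length and a complete tally by type from the first patient to the last. Publication in April 2021 cannot have revealed the length for patients allocated before then.
- **That delaying a patient by a day is enough to change the arm.** Delay leaves the next envelope as it is unless another patient of the same type is enrolled in between. No accrual rate is given. Assuming 384 patients over 2 to 5 years, split equally by type, the daily chance of such an enrolment is 1 − exp(−192/730) = 23% down to 1 − exp(−192/1825) = 10%. Not approaching a patient remains possible, but much of eligibility is objective (lipids, liver enzymes, earlier statin use, coronary history).
- **That nothing can be done in analysis.** Age, blood pressure, heart rate, history and laboratory values are recorded at enrolment, so imbalance can be examined and partly adjusted for. Severity that is not recorded would remain.

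**Conclusion.** The point holds as a vulnerability in a stated design choice. A fixed block length of 4, in an unblinded trial at one hospital and published during recruitment, undermines the envelopes. For a recruiter who knows the length and tallies by type, up to 33.3% of assignments are certain (at most about 128 of 384, fewer if the length became known part-way), and 70.8% can be guessed correctly. These proportions are exact. That anyone uses them in this trial is not shown, and the size of any resulting bias in mortality cannot be estimated from the document. Because entry rests partly on clinical judgement related to early death, and adjustment for recorded baseline values would correct only part of any bias, the weakness should be removed for the assignments still to be made. The sample size is unaffected.

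**What to change.** For assignments still to be made:

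1. The separate staff complete any part-filled block from the existing list. This leaves at most three assignments per type, six in all, on the old scheme. Envelopes already opened stand.
2. They then regenerate the unused envelopes within each type with randomly varying block lengths, for example 4, 6 and 8.
3. The lengths are withheld from recruiters and from public documents until recruitment ends. The public text says only that they vary at random.
4. Each envelope is opened only after consent and eligibility have been recorded for that patient.

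Certain prediction falls from 33% to about 2% (5.5% with lengths 4 and 6 only). Best-guess success falls only from 70.8% to about 68–69%, so the change should not be presented as making the sequence unguessable. Step 4 adds protection because the decision to enrol is on record before the arm is revealed, although it cannot prevent a patient from never being approached.

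The cost is one new list, repacked envelopes and a protocol amendment through the approval route that the Amendment section already sets out. The arms may also differ by a few more patients: an unfinished block of 8 can leave a difference of at most 4 within a type, against 2 with blocks of 4.
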